**Method and design:**

This will be an open-label, 2-armed, randomized, phase-II single-center trial of LNG-IUD plus metformin or megestrol acetate (MA) plus metformin. A total of 88 participants will be randomly assigned into 2 treatment arms in a 1:1 ratio. Clinical, laboratory, ultrasound and radiology data, will be collected at baseline, and then at 3, 6, 9, 12, 18, and 24 months. EC biomarkers will be collected at baseline. The primary aim is to determine the efficacy of a levonorgestrel-releasing intrauterine device (LNG-IUD) plus metformin, or megestrol acetate (MA) plus metformin in achieving pathological complete response (pCR) at 12 months, as well as post-treatment pregnancy outcomes and recurrence rate. The secondary aims are to predict the response to an LNG-IUD plus metformin and MA plus metformin via clinical, blood, and tissue predictive biomarkers.

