However, the outcomes of treatment with an LNG-IUD plus metformin, or MA plus metformin have not been compared. The primary aim of this phase II, 2-arm randomized trial is to determine the effectiveness of an LNG-IUD (Mirena®) plus metformin, and MA plus metformin to achieve a pathological complete response (pCR) at 12th months, pregnancy outcomes, and recurrence rates. The secondary aim is to predict the response to treatment with an LNG-IUD plus metformin, and MA plus metformin using clinical data and blood and tissue predictive biomarkers.

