### Criteria for discontinuation of trial treatment

The criteria for the discontinuation of a trial medication are as follows:A participant declines further participation or withdraws their consent.Cancelation of the entire study.The protocol treatment will be stopped if it does not result in remission according to the following criteria: no treatment response or pCR by 1 year; disease progression at any time; relapse after remission.Severe adverse events (progressive or persistent) which may be related to the medication (such as hemorrhagic shock due to massive vaginal bleeding, severe allergy, thrombosis, liver function damage) and newly diagnosed other malignancy (e.g., breast cancer) will be evaluated by 2 chief physicians before the trial is stopped.Any situation in which the LNG-IUD, MA, or metformin treatment cannot be continued according to the judgment of the physician.

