### Efficacy assessments

Assessments of effectiveness will be performed at 3, 6, 9, 12, 18, and 24 months after beginning treatment, including weight loss, histological examination of endometrial tissue specimens, and pregnancy outcomes. The total study duration will be 2 years.Weight loss of patients in the 2 groups will be evaluated.Hysteroscopic endometrial curettage will be performed to rule out disease progression (Fig. 2).Complete pathological response is defined as 2 consecutive negative endometrial biopsies. Endometrial tissue for pathological examination will be obtained during hysteroscopy. Tissue pathological examination will be performed in a double-blind manner by 2 senior pathologists. A third pathologist will be consulted if the results are inconsistent.A.If the disease progresses, such as atypical hyperplasia to endometrial cancer, well-differentiated adenocarcinoma of the endometrial to moderately or poorly differentiated endometrial cancer, or other types of endometrial cancer, hysterectomy will be recommended.B.If complete remission is achieved (2 consecutive negative endometrial biopsies), the patient will be recommended to remove the LNG-IUD or discontinue oral progesterone. Patients will continue to take metformin and monitor ovulation if pregnancy is desired. Participants who are not pregnant will be followed-up every 3 months for endometrial biopsy. Patients with a successful pregnancy and delivery who desire to retain reproductive function will undergo regular endometrial biopsies and imaging studies.C.If there is no response to treatment, but no progression or partial response, the current treatment will be continued; assessments and efficacy evaluations will be performed every 3 months. If there is progression or recurrence after remission, the patient will be recommended to terminate participation in the trial. If the assessments continue to indicate no response or partial response, assessments will be continued every 3 months for 12 months. If assessment at 12 months indicates an incomplete response, the patient will be recommended to terminate participation in the trial.D.If EC develops during follow-up after a complete response, it will be considered a recurrence and surgical treatment will be recommended.E.If there is no improvement or partial response after 12 months of treatment, the patient will be informed of the risks of continuing conservative treatment and a hysterectomy will be recommended.Pregnancy assessment: outcomes of abortion, premature delivery, and full-term delivery will be recorded.

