### Statistical analysis

The EHA and EC pCR rates and 95% CIs will be calculated for both groups. Patient’s quality of life will be assessed at baseline, week 1, and at 3, 6, 9, 12, 18, and 24 months. Other data acquisition and analyses will include the complete response rate for the trial treatment period; the rate of trial continuation for the LNG-IUD plus metformin and MA plus metformin groups; BMI values and homeostatic model assessment of insulin resistance (HOMA-IR) results of all response cases that wish to become pregnant; the proportion of patients that become pregnant at least once during the trial period; pregnancy outcomes (miscarriage, stillbirth, live birth, and weeks of gestation); and the proportion of patients that give birth to a child. Data will be reported as mean and standard deviation (SD), median and interquartile range (IQR), or number and percentage (%) based on if the data are continuous or categorical and on the normality assumption. The Kolmogorov–Smirnov normality test will be used to check the normality of continuous variables. For comparisons between 2 groups, Student’s t-test or the Mann–Whitney U test will be used according to the normality assumption. The Chi-square test will be used to compare the number of cases and percentage between groups.

This study will also investigate changes in the expression of molecular biomarkers. Since the changing results over time are repeated measurements, statistical tests of dependent data, such as the paired t-test or mixed-design ANOVA will be used.

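### A crude recurrence percentage gives responders 12 to 18 months of observation after pCR depending on when they respond, so it would overstate recurrence in whichever arm responds sooner

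*Protocol article*

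**What the plan says.** **Aim.** The Abstract lists pCR at 12 months "as well as post-treatment pregnancy outcomes and recurrence rate" as the primary aim. The Introduction repeats "pregnancy outcomes, and recurrence rates", and the Discussion names recurrence among the endpoints.

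**Response and recurrence.** Efficacy assessments states: "Complete pathological response is defined as 2 consecutive negative endometrial biopsies". The same section says: "If EC develops during follow-up after a complete response, it will be considered a recurrence".

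**Timing.** "Assessments of effectiveness will be performed at 3, 6, 9, 12, 18, and 24 months after beginning treatment", and "The total study duration will be 2 years". Under Criteria for discontinuation of trial treatment, protocol treatment stops if there is "no treatment response or pCR by 1 year".

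**Analysis.** The Statistical analysis section gives one rule for counts: "The Chi-square test will be used to compare the number of cases and percentage between groups". It names no time-to-event method and does not mention recurrence. The Sample size section says that women who become pregnant leave the study and count as not having recurred, which treats recurrence as a yes/no case.

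**The concern.** Recurrence can be observed only after pCR, but the visits and the end of study are counted from the start of treatment. A woman confirmed early is therefore watched longer for relapse than one confirmed late. A chi-square test on a percentage gives both the same weight.

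The arms compare a local with a systemic progestin, and the Discussion asks whether their effects differ, so different speeds of response are plausible. If they do differ, the faster arm is expected to show more recurrences at an identical hazard. A favourable property would then be reported as an unfavourable one, on an outcome that the article presents as distinguishing this trial from others.

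**Working it through.** **The plan's own figure.** No recurrence figure is given. The stated sample size reproduces: with w = 0.3, two-sided alpha 0.05 and power 0.80, N = (1.960 + 0.842)² / 0.3² = 87.2, rounded up to 88 for equal arms. It is not affected by this point.

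**Step 1: scheduled time at risk.** Biopsies fall at months 3, 6, 9 and 12, and two consecutive negatives are needed. Confirmation is therefore at month 6 (3+6), 9 (6+9) or 12 (9+12).

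Window = 24 − month of confirmed pCR = 18, 15 or 12 months.

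The longest window exceeds the shortest by 18/12 − 1 = 50%. If pCR were dated at the first negative biopsy, the windows would be 21, 18 or 15 months, with the same 6-month spread.

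**Step 2: crude recurrence at a common hazard.** The documents give no hazard, so assume a constant one, equal in both arms, set by a 12-month recurrence risk p. The risk over a window of T months is 1 − (1 − p)^(T/12).

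| p | T = 18 | T = 15 | T = 12 |
|---|---|---|---|
| 10% | 14.6% | 12.3% | 10.0% |
| 20% | 28.4% | 24.3% | 20.0% |
| 30% | 41.4% | 36.0% | 30.0% |

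**Step 3: average over response times.** The mixes (percentage of responders confirmed at months 6/9/12) are assumptions. For 70/20/10 at p = 20%: 0.7 × 28.4 + 0.2 × 24.3 + 0.1 × 20.0 = 26.8%. For 10/20/70: 0.1 × 28.4 + 0.2 × 24.3 + 0.7 × 20.0 = 21.7%. The ratio is 1.23.

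| Faster v slower arm | Crude recurrence, p = 20% | Ratio, p from 10% to 30% |
|---|---|---|
| 40/30/30 v 30/30/40 | 24.7% v 23.8% | 1.03–1.04 |
| 50/30/20 v 20/30/50 | 25.5% v 23.0% | 1.10–1.12 |
| 70/20/10 v 10/20/70 | 26.8% v 21.7% | 1.21–1.25 |
| 100/0/0 v 0/0/100 (bound) | 28.4% v 20.0% | 1.38–1.46 |

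The true difference at 12 months after pCR is zero in every row.

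**Step 4: effect on the test.** A pCR rate of 60%, the figure that the Sample size section assumes for MA alone, gives about 26 responders per arm (0.60 × 44 = 26.4). In simulation with 12-month risks from 10% to 40%, the chi-square test rejected in about 5–6% of runs with equal windows, 6–7% with 70/20/10 v 20/30/50, and 8–16% in the bounding case.

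**Step 5: pregnancy.** Pregnancy can shorten the window below 12 months while the woman still counts as not recurring. At p = 20% with response times spread evenly, crude recurrence is 24.3% without pregnancies. An assumed 12-month pregnancy probability of 20% lowers it to 21.3%, and one of 40% to 18.1%, at an unchanged recurrence hazard.

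**Step 6: can a 12-month horizon be observed?** The passages on biopsies after remission disagree:

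- Table 1 lists hysteroscopy and D&C at months 18 and 24 only.
- Efficacy assessments (item B, for women who are not pregnant) and Table 1 footnote b have them every 3 months.
- Follow-up evaluations puts the visit after month 18 one year later, which is month 30, although it also describes a month-24 visit.

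On the Table 1 schedule, a woman confirmed at month 9 reaches 12 months after pCR at month 21, when no biopsy is listed. A relapse after month 18 would be found at month 24, beyond the horizon.

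**The case against.** The strongest reply is that the article commits no error. The chi-square sentence is a general line for categorical data, recurrence is absent from the outcomes listed around it, and the time origin, censoring and estimator are matters that an unseen analysis plan may settle. Part of this stands. A reader might infer that the protocol prescribes a chi-square test for recurrence on a clock started at treatment. It does not say so: only the visits are timed from treatment, and recurrence is defined as arising after a complete response. What remains is that recurrence is in the primary aim, is counted as yes or no in the Sample size section, and falls under the only comparison rule given for cases and percentages.

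A second reply is that the size depends on assumptions. This also stands. No response times or hazards are given, and the ratio of 1.23 needs mirror-image timing. With 26 responders per arm, 26.8% v 21.7% is about one woman (26 × 0.051 = 1.3). The Discussion also says that the design is not confirmatory.

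A third is that the pregnancy rule may matter more than the clock. It can: the fall from 24.3% to 18.1% exceeds the 5.1-point gap in the large-difference mix. It is a reason to settle both together.

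Finally, Follow-up evaluations allows a complete response at month 3 and a recurrence at month 6, which does not fit earliest confirmation at month 6. An earlier response date would widen the spread, so this affects the exact range and not the direction.

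**Conclusion.** The point holds in a limited form. If recurrence is compared as a crude percentage, as the stated rule implies, the result depends on the speed of response, because scheduled time at risk is 18, 15 or 12 months. The bias between arms requires that they differ in time to pCR, and it then runs, in expectation, against the faster arm. On the assumed constant and equal hazard, the ratio is about 1.03 for a small timing difference, 1.10 to 1.12 for a moderate one and about 1.2 for a large one.

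A reader might go further and infer a badly inflated type I error, or that a spurious recurrence difference is likely. The figures do not support that: at this sample size rejection stays at 6–7% except in the bounding case, so the main harm is to the estimate. The change should be made because recurrence is in the primary aim and the remedy is cheap. The sample size is unaffected.

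**What to change.** 1. Define time to recurrence from the date of confirmed pCR.
2. Estimate and compare it between arms with a time-to-event method that allows for detection at visits: an interval-censored analysis, or Kaplan-Meier or cumulative incidence with a log-rank or Gray test. Use the 12-month post-pCR estimate as the summary.
3. Replace the rule that counts pregnancies as non-recurrence. State whether pregnancy is a censoring event or a competing event. The two answer different questions, so one should be named in advance.
4. Before fixing the horizon, reconcile Table 1, its footnote b, Efficacy assessments and Follow-up evaluations on biopsy timing after remission, since they decide when a recurrence can be seen. The ±14-day visit windows also mean that some women confirmed at month 12 will fall slightly short of 12 months.

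**Cost.** Items 1 to 3 change analysis wording and add some analysis work. Item 4 is a protocol clarification, and whether it changes the number of biopsies depends on how the passages are reconciled. Recurrences later than 12 months after pCR in early responders enter the curve but not the 12-month estimate.

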**Fig. 1 Fig1:**
[figure not shown]
Trial design. pCR, pathological complete response

The trial will only include women with early-stage EC. The criteria for early-stage EC are: (1) stage 1 disease (absence of lymphadenopathy or pelvic masses); (2) endometrioid cell type and International Federation of Obstetrics and Gynecology (FIGO) grade 1 disease; (3) no evidence of lymph vascular space invasion on examination of curettage specimens; (4) absent or only minimal myometrial invasion (depth of infiltration < 1/2 muscle thickness on magnetic resonance imaging [MRI] to exclude deeply invasive cancers); (5) serum cancer antigen (CA)125 level ≤ 30 U/mL [31].

Through strict patient inclusion criteria, we expect to control the probability of disease progression in trial patients at 3%. All patients will receive examinations and laboratory and imaging studies at baseline and 3, 6, 9, 12, 18, and 24 months after starting treatment.

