### Follow-up evaluations

At the 3-month follow-up, if endometrial pathology shows progressive disease, the patient will be withdrawn from the trial. If the endometrial pathology indicates a complete response, partial response, or stable disease, the patient will be followed-up after 3 months. At the 6 month follow-up, if the endometrial pathology shows progressive disease or recurrence, the patient will be withdrawn from the trial. If the pathology shows a complete response, partial response, or stable disease, the patient will be followed-up after 3 months. At the 9-month follow-up, if the endometrial pathology shows progressive disease or recurrence, the patient will be withdrawn from the trial. If the pathology shows a complete response, partial response, or stable disease, the patient will be followed-up after 3 months. At the 12-month follow-up, if the endometrial pathology shows a partial response, progressive disease, stable disease, or recurrence, the patient will be withdrawn from the trial. If the pathology shows a complete response, the patient will be followed-up in 6 months. At the 18-month follow-up, if the endometrial pathology shows an incomplete response, the patient will be withdrawn from the trial. If there is a complete response, the patient will be followed-up after 1 year. At the 24-month follow-up, if the endometrial pathology shows an incomplete response, the patient will be withdrawn from the trial. In the case of a complete response, the patient will continue to be followed long-term.

The study duration is 2 years, but the treatment and follow-up of patients will be long-term. A hysterectomy will be recommended for patients who have a complete response and have completed childbirth. Patients who have fertility requirements or are unwilling to undergo a hysterectomy will be followed closely for signs of recurrence.

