### Sample size

According to a previous study, the mean pCR rate for LNG-IUD alone was 68% (95% confidence interval [CI]: 45–86%) [30], it was assumed that the rate in the MA-alone group will be 60%. Based on a prior study [38], we anticipate that the true pCR rate will be closer to the lower confidence limit of 45%. Patients who become pregnant during the trial will be withdrawn from the study and treated as non-recurrence in-trial cases.

The sample size was estimated by software G*Power version 3.1 (Heinrich-Heine-Universität Düsseldorf, Düsseldorf, German). The effect size, w, of the 2-group contingency table was set at a medium level of 0.3, type I error (alpha) at 0.05, 2-tailed, and power was set at 0.80, chi-square test. The size ratio between the 2 groups was set at 1:1. The estimated minimum required sample size of each group is 44, and the total sample size is 88.

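### Mixed-design ANOVA needs complete visits, but the withdrawal rules leave only responders at months 18 and 24; use a mixed model to month 12 and describe later visits separately

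*Protocol article*

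**What the plan says.** The Statistical analysis section announces that "This study will also investigate changes in the expression of molecular biomarkers" and, because such results are repeated measurements, that "statistical tests of dependent data, such as the paired t-test or mixed-design ANOVA will be used". It fixes no visit window for these tests.

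The visit plan, in the Design section, is: "All patients will receive examinations and laboratory and imaging studies at baseline and 3, 6, 9, 12, 18, and 24 months after starting treatment". Table 1 marks CA125, HE4, HbA1c, weight and BMI at baseline and at every one of these visits. The Statistical analysis section schedules quality of life to month 24 as well.

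The Follow-up evaluations section sets who is still there to be measured:
- Month 3: "At the 3-month follow-up, if endometrial pathology shows progressive disease, the patient will be withdrawn from the trial". At months 6 and 9 progression or recurrence has the same effect.
- Month 12: "if the endometrial pathology shows a partial response, progressive disease, stable disease, or recurrence, the patient will be withdrawn from the trial".
- Month 18: "At the 18-month follow-up, if the endometrial pathology shows an incomplete response, the patient will be withdrawn from the trial".

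The Sample size section adds: "Patients who become pregnant during the trial will be withdrawn from the study".

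The Efficacy assessments section words the month-12 rule more softly: women with an incomplete response are advised to end participation.

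The only rules for the outcomes of withdrawn women concern yes/no results (counted as non-pCR under Treatment of adverse events, as non-recurrence under Sample size). None concerns a repeated measurement.

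**The concern.** Classical mixed-design (split-plot) ANOVA needs a value from each woman at each visit in the analysis, and a woman who lacks one is dropped altogether. A paired t-test needs only the two visits compared. Here the missing visits are written into the protocol and depend on the pathology result. After month 12 no woman without complete response remains, so an ANOVA that reaches month 18 or 24 is an analysis of responders, and the values that non-responders gave from baseline to month 12 are thrown away.

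At stake are the secondary series taken at every visit. Efficacy assessments lists weight loss in the two groups among the effectiveness results, and the Discussion promises an evaluation of metabolic improvement. Both are questions about all treated women, and an analysis of sustained responders answers a different one.

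**Working it through.** **1. The protocol's own sample size.** Inputs (Sample size section): w = 0.3, two-sided alpha 0.05, power 0.80, chi-square test, 1:1. With 1 degree of freedom, N = (1.960 + 0.842)² / 0.3² = 87.2, which rounds up to 88. The noncentral chi-square gives power 0.8035 at N = 88 and 0.7991 at N = 87. The stated 88 (44 per arm) reproduces and is not touched by this point.

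**2. Who can have month-18 or month-24 values.** Only women in complete response at month 12 go on. Taking the pCR rate as that proportion, the expected number is at most 88 × pCR rate.

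| pCR rate | Source | Can go on | Cannot |
|---|---|---|---|
| 45% | Sample size, lower limit | 39.6 | 48.4 |
| 57% | Introduction, LNG-IUD plus metformin in an earlier trial | 50.2 | 37.8 |
| 60% | Sample size, MA alone | 52.8 | 35.2 |
| 68% | Sample size, LNG-IUD alone | 59.8 | 28.2 |

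With 60% in one arm and 45% in the other: 44 × 0.60 + 44 × 0.45 = 46.2.

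Recurrence and pregnancy lower these numbers. The protocol gives no rate for either. If 10% to 30% of responders leave for these reasons (assumption), the range runs from 88 × 0.45 × 0.70 = 27.7 to 88 × 0.68 × 0.90 = 53.9.

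**3. Who has values up to month 12.** Women with partial response or stable disease are kept at months 3, 6 and 9 and leave on the month-12 pathology, so they have a month-12 visit. With the 3% progression expected in the Design section, 88 × 0.97 = 85.4 women reach month 12, before pregnancies, recurrences and other withdrawals are counted.

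**4. What selection could do (illustration only).** If responders and non-responders differ in mean change by g SD, a responders-only mean differs from the all-randomised mean by (1 − pCR rate) × g. For g from 0.25 to 1.0 (assumption):
- pCR 45%: 0.55 × g = 0.14 to 0.55 SD
- pCR 68%: 0.32 × g = 0.08 to 0.32 SD

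If change depends on response alone and the arms have 60% and 45%, the true arm difference is 0.15 × g, and among responders it is 0.

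A simulation of 4,000 trials (44 per arm, 60% v 45%, g = 1, about 3% progressing) agreed. On average there were 46.2 responders, and 85.3 women were seen at month 12. Mean change was −0.525 SD in all women, −0.542 in those seen at month 12 and −0.999 in responders. The arm difference was −0.145 SD in all women and 0.004 in responders. Nearly all of the distortion enters after month 12.

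**The case against.** The strongest reply is that the protocol never specifies an ANOVA over the whole schedule. The tests are given as examples, no window is fixed, and an analysis plan that is not shown could set the window or name another method. That stands as a limit: the fault arises only if month 18 or 24 enters the analysis. But the protocol chose to name these tests, and the one meant for several visits fits its own withdrawal rules badly.

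A reader might infer more than this, and the documents do not support it:
- **That both tests lose all non-responders.** A paired test from baseline to month 3, 6, 9 or 12 keeps women with partial response and stable disease, as does an ANOVA confined to months 0 to 12 apart from early exits.
- **That the response-prediction aim is damaged.** The Abstract states: "The secondary aims are to predict the response to an LNG-IUD plus metformin and MA plus metformin via clinical, blood, and tissue predictive biomarkers". It places EC biomarker collection at baseline. Tests of change within women neither serve nor harm that aim.
- **That the sentence plainly governs CA125 or weight.** It follows one on molecular biomarkers. Table 1 marks biomarker blood at baseline only, and its receptor row as shown has no visit marked. Whether such markers are resampled is a separate question. In practice the point bears on series taken at every visit and on any marker actually measured repeatedly.
- **That a definite bias can be quoted.** The shifts above come from assumed effects. With g = 0.5 the arm difference would be 0.15 × 0.5 = 0.075 SD. With a correlation of 0.6 between visits (assumption), its standard error with all 88 women is about √(2 × 0.4) × √(2/44) = 0.19 SD, so no method would detect it.

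Pregnancies are also followed to their outcome, and biopsies and imaging continue after delivery. That softens the pregnancy exit, but it does not say that the marker series continue.

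**Conclusion.** The point holds in a limited form. A mixed-design ANOVA that includes month 18 or 24, or a paired test using either visit, describes only responders still in follow-up: at most about 40 to 60 of 88 women at pCR rates of 45% to 68%. The ANOVA also discards non-responders' observed values up to month 12. This follows from the withdrawal rules as worded under Follow-up evaluations and Sample size, from reading the ANOVA in its classical complete-case form, and from equating the pCR rate with complete response at month 12.

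The direction and size of any bias depend on how responders and non-responders differ, which the protocol does not say. The primary pCR comparison, the sample size and the prediction aim are unaffected. Minor; secondary analyses only.

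**What to change.** Replace mixed-design ANOVA with a linear mixed model for repeated measures (REML, unstructured covariance), using all available visits from baseline to month 12 in all randomised women. Include visit, arm, arm-by-visit, the baseline value and diagnosis (EHA or EC), and make month 12 the main contrast. Paired tests of change from baseline to a visit up to month 12 can stay.

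Report months 18 and 24 separately and descriptively, as values among responders still in follow-up. They should not be presented as model estimates for all randomised women: a model run through month 24 would extrapolate to non-responders who are by rule never measured there, and its estimates would not be responder means either.

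The month-12 rule must be reconciled between Efficacy assessments (advised to end participation) and Follow-up evaluations (withdrawn), because it decides who has later data.

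Cost: a few sentences, with no new data and no change in sample size. The downside is that the model assumes data are missing at random given what was observed. Exit is decided by pathology, which is not in the model, so the assumption is not assured. Up to month 12 few exits for progression are expected; those for recurrence and pregnancy cannot be sized from the protocol.
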